### Family-centered care program (FamilieNetz)

Following the increased knowledge about the adverse consequences of preterm birth on child and family, but also on the healthcare system, different psychosocial interventions for parents of preterm infants have been developed with the aim to improve the early parent-child-relationship and reduce parental stress [30–35]. However, existing interventions in Germany are not standardized and have not been evaluated rigorously, making it difficult to draw firm conclusions on their preventive effects [36–38].

A novel support and training program for families of sick newborns and preterm infants (FamilieNetz) was developed and introduced in clinical routine at the Department of Neonatology and Pediatric Intensive Care at the University Hospital Carl Gustav Carus, Dresden in 2009. The comprehensive program consists of different interventions, including parent counseling, parent education and discharge planning. Its philosophy focuses on empowering parents in primary caregiving for their child and involving them in daily routine as early as possible by giving them psychological and social-medical support during the initial hospital stay [39].

Single components of the intervention program have been evaluated and as a consequence health insurance companies in Saxony are compensating it in part since 2012. In a next step, the program shall be introduced into other perinatal centers in Saxony and later in Germany as well. However, prior to the introduction, a comprehensive evaluation of the whole multiple component approach is required, in accordance with the principles of evidence-based healthcare.

In order to address the issues outlined above, the study EcoCare-PIn will examine the following research questions:What are the short- and long-term consequences of preterm birth with regard to parental stress, parent-child relationship, family and child quality of life, child development, and healthcare utilization including costs?Does early family-centered psychosocial care prevent the hypothesized negative consequences of preterm birth on parental stress, parent-child relationship, family and child quality of life, child development, and healthcare utilization including costs?

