## Methods/Design

EcoCare-PIn is a cohort study comprising the linkage of individual-level data from two different sources: (1) administrative claims data from the German statutory health insurance AOK PLUS on all insured children born between 2007 and 2013 in Saxony and (2) primary data collected by means of questionnaires (in 2014/2015) from parents or legal caregivers of VLBW (very low birth weight) infants (<1,500 g), LBW (low birth weight) infants (1,500 to 2,499 g), and infants with a birth weight of 2,500 g or higher as controls.

Preterm birth is generally defined as birth before 37 completed weeks of gestation [2]. As there is considerable overlap between gestational age under 37 weeks and birth weight below 2,500 g, the use of birth weight (<2,500 g) for the definition of preterm born children instead of gestational age (<37 weeks) can be regarded as an acceptable approach in case that data on gestational age are not available or of uncertain quality [40, 41]. As the AOK PLUS does not provide data on gestational age, but on birth weight, we will use the latter as proxy measure for preterm birth.

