### Design and recruitment

The study is based on pseudonymized *administrative outpatient and inpatient data* of all children born in Saxony between January 1^st^, 2007 and December 31^st^, 2013 with health insurance at the AOK PLUS. The whole cohort of newborns will include almost 140,000 children, with approximately 1,000 VLBW- and 5,500 LBW-children among them. A broad set of insurance data will be provided and analyzed within this study, including birth weight (classified into <1,500 g (VLBW), 1,500–2,499 g (LBW) and ≥2,500 g (controls)), selected sociodemographic characteristics of children (age, sex, first three digits of ZIP code), diagnoses (ICD-10 codes), diagnosis related billing information (DRG-codes), prescriptions (PZN-codes, ATC-codes, cost), medical procedures (OPS-codes), claim codes for outpatient services and procedures (EBM-codes) and data of healthcare providers (discipline, first three digits of ZIP code) [42]. Based upon these pseudonymized administrative data, we will investigate and compare VLBW-, LBW- and control children with regard to mental and physical development, healthcare utilization and cost from birth through December 31^st^, 2013.

To enable further analyses, additional *primary data* will be collected on a subgroup of the described cohort of children. With support from the AOK PLUS, parents or legal caregivers from all preterm born children and parents/legal caregivers of a matched sample of 10,000 control children will be approached via postal questionnaires. Control children for the primary data collection will be selected via frequency matching according to birth year, sex and administrative district.

The questionnaire will cover information on parental stress, parent-child relationship, child’s physical and mental development (including school performance), quality of life of children, family quality of life, sociodemographic characteristics of parents, and exposure to psychosocial care in the neonatal period. These primary data will be linked to the administrative data on an individual level.

Figure 2 provides a flow chart on the design of the study.

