### Procedures of data collection

The fundamental principle of the data concept, which will be outlined below, is to strictly separate the sites of data collection from the data analysis site.

Starting point is the site of data collection I (AOK PLUS), which submits pseudonymized (pseudonym I) outpatient and inpatient data of all children born in Saxony between January 2007 and December 2013 with health insurance at the AOK PLUS to the data analysis site (Center for Evidence-Based Healthcare (ZEGV)).

Data analysis site (ZEGV) will then identify individuals eligible for the primary data collection and gives pseudonyms (pseudonym I) of all VLBW and LBW children as well as of matched control children to the site of data collection I (AOK PLUS). For reasons of better practicability, ZEGV additionally transfers a new short pseudonym per individual (pseudonym II).

Data collection site I (AOK PLUS) de-pseudonymizes these information and sends questionnaires with pseudonym I and II to the parents or legal caregivers of the selected AOK PLUS members. Each questionnaire is supplemented by a) a detailed study information explaining study objectives, study design and data protections issues, and b) an informed consent form.

AOK PLUS members whose caregivers agree with study participation send the completed questionnaire and the signed consent form to the data collection site II (KKS).

The data collection site II (KKS) will receive the completed questionnaires and consent forms. Only questionnaires accompanied by a validly signed consent form will be considered for the study. KKS will delete any personal identifiers from those datasets, pseudonymize them and send them to the data analysis site (ZEGV) for the linkage with administrative data and statistical analysis. Throughout the study, the site of data analysis (ZEGV) will only use pseudonymized data.

The process of data collection is summarized in Fig. 3.

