### Statistical analysis

Multivariate binary or multinomial logistic regression models as well as multiple linear regression models will be used to analyze the effect of birth weight (differentiated into VLBW, LBW and birth weight ≥ 2,500 g) on the outcomes. Adjustment will be made for sex, year of birth and socioeconomic status. Modification of the presumed adverse short and long-term effects of preterm birth through early psychosocial care will be analyzed by modeling the exposure to such a program as predictor for parental stress, parent-child relationship, quality of life, child development, healthcare utilization and costs. Effect modification will be explored by including the corresponding interaction-terms in the regression models. With an expected response rate of 30 % and an expected power (1-β) of 80 %, effect sizes (Cohen’s f) of 0.045 or higher can be detected at a 5 % significance level in analyses with the linked dataset (see Fig. 4). For analyses based on the whole administrative data cohort, effect sizes (Cohen’s f) of 0.035 or higher can be detected with a power of 80 % at the 5 % significance level.

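### Administrative district is used to match controls but is missing from the stated adjustment set; this matters mainly for the unmatched whole cohort and the programme effect

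*Protocol article*

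**What the plan says.** All references are to the protocol article.

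- **Matching** (Design and recruitment): "Control children for the primary data collection will be selected via frequency matching according to birth year, sex and administrative district". This covers the questionnaire sample only. The claims analyses use every child in the insurer's birth cohort.
- **Adjustment** (Statistical analysis): "Adjustment will be made for sex, year of birth and socioeconomic status". The sentence directly follows the description of the birth-weight models.
- **Programme effect** (Statistical analysis): the plan is "modeling the exposure to such a program as predictor for parental stress, parent-child relationship, quality of life, child development, healthcare utilization and costs", with interaction terms to explore effect modification. No separate covariate list is given.
- **Place data held**: the claims file includes "selected sociodemographic characteristics of children (age, sex, first three digits of ZIP code". The analysis site selects the questionnaire sample itself: it "gives pseudonyms (pseudonym I) of all VLBW and LBW children as well as of matched control children" to the insurer (Procedures of data collection).
- **Where the programme runs** (section on FamilieNetz): it entered routine care at the "Department of Neonatology and Pediatric Intensive Care at the University Hospital Carl Gustav Carus, Dresden in 2009". For other centres: "In a next step, the program shall be introduced into other perinatal centers in Saxony and later in Germany as well".
- **Region covered** (Methods/Design): "all insured children born between 2007 and 2013 in Saxony".

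**The concern.** By matching on district, the authors treat place as something that could distort a comparison. The adjustment set then keeps the other two matching factors and drops this one without giving a reason. How much that matters depends on the analysis.

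1. **Whole administrative cohort.** The controls are unmatched, so place is handled neither by design nor by the stated model. The outcomes are utilisation, cost and coded diagnoses, which can vary with local supply and coding practice.
2. **Programme effect.** Matching balances birth-weight groups, not exposed and unexposed families. With one hospital running FamilieNetz and a cohort drawn from all of Saxony, residence plausibly governs access. A regional outcome difference could then be read as a benefit or harm of the programme.
3. **Linked birth-weight comparison.** Matching removes most district confounding at invitation. What remains is drift through non-response, and the fact that matching to the preterm group as a whole need not balance the VLBW and LBW groups separately.

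**Working it through.** **1. The two lists side by side**

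| Factor | Matching | Adjustment |
|---|---|---|
| Sex | yes | yes |
| Birth year | yes | yes |
| Administrative district | yes | no |
| Socioeconomic status | no | yes |

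No other section adds district, ZIP code, region or treating hospital as a covariate.

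**2. The plan's own figure**

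Expected linked sample: 0.30 × (1,000 + 5,500 + 10,000) = 4,950. For three birth-weight groups (2 numerator degrees of freedom), α = 0.05 and noncentrality λ = f² × N, 80 % power is reached at f = 0.0441. Power at f = 0.045 is 81.6 %. The stated 0.045 reproduces.

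**3. Cost of adding district to the birth-weight models**

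Assume 11 model degrees of freedom (group 2, sex 1, year 6, socioeconomic status 2) and add 0 to 28 for district. Detectable f stays at 0.0441 and power at f = 0.045 stays at 81.6 %. This gives no credit for outcome variance that district might explain.

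**4. Linked birth-weight comparison**

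Assume a 10-point district imbalance among respondents and a 0.1 SD regional outcome difference: 0.10 × 0.1 = 0.01 SD. The detectable LBW versus control difference is 2.802 × √(1/1,650 + 1/3,000) = 0.086 SD, so the bias is about one eighth of it.

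**5. Programme effect (illustration, all inputs assumed)**

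Let q be the share of families near the centre, e₁ the exposure proportion near the centre and e₀ that elsewhere. Let D be the regional outcome difference left after the stated adjustment.

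- Overall exposure: p = q·e₁ + (1 − q)·e₀
- Near-centre share among exposed: A = q·e₁ / p
- Near-centre share among unexposed: B = q·(1 − e₁) / (1 − p)
- Spurious effect: D × (A − B)
- Share of exposure variance explained by place: R² = q(1 − q)(e₁ − e₀)² / [p(1 − p)]
- Standard-error factor after adjusting for place: 1/√(1 − R²)

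| q | e₁ | e₀ | p | A | B | Bias at D = 0.10 SD | R² | SE factor |
|---|---|---|---|---|---|---|---|---|
| 0.2 | 0.3 | 0.05 | 0.100 | 0.60 | 0.16 | 0.044 | 0.11 | 1.06 |
| 0.2 | 0.5 | 0.05 | 0.140 | 0.71 | 0.12 | 0.060 | 0.27 | 1.17 |
| 0.2 | 0.6 | 0.02 | 0.136 | 0.88 | 0.09 | 0.079 | 0.46 | 1.36 |
| 0.3 | 0.3 | 0.05 | 0.125 | 0.72 | 0.24 | 0.048 | 0.12 | 1.07 |
| 0.3 | 0.5 | 0.05 | 0.185 | 0.81 | 0.18 | 0.063 | 0.28 | 1.18 |
| 0.3 | 0.6 | 0.02 | 0.194 | 0.93 | 0.15 | 0.078 | 0.45 | 1.35 |

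The bias is 0.04 to 0.08 SD at D = 0.10. It scales with D: about 0.02 to 0.04 SD at D = 0.05 and 0.09 to 0.16 SD at D = 0.20.

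**6. A comparator for the programme contrast**

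Assume the contrast is made among preterm respondents: 0.30 × 6,500 = 1,950. Detectable d = 2.802 / √(1,950 × p(1 − p)). At p = 0.100 this is 0.21; at p = 0.194 it is 0.16. Row by row, the bias at D = 0.10 is 21 % to 49 % of the detectable effect.

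**The case against.** - **This is a matched cohort, not a case-control study.** Controls are chosen by birth-weight group, which is the exposure. Matching then removes most district confounding at selection, and carrying every matching factor into the model is good practice rather than a condition of validity. This stands, and it makes the linked birth-weight comparison the weakest part of the point.
- **The programme models have no stated covariate list.** A reader might infer that district is excluded from every regression. The article supports only that no model is stated to include it. A condensed article may leave the programme model's covariates to a fuller document. The adjustment list for the birth-weight models, however, is stated and omits place.
- **Exposure may not be confined to one centre.** A reader might infer that exposure is close to zero far from Dresden. The article gives no exposure by district. The questionnaire asks about neonatal psychosocial care in general, and the background mentions other, non-standardised interventions. The link between residence and access is an inference from the single programme site.
- **Availability of district is inferred.** The listed claims field is the three-digit ZIP code. That district can be assigned follows from its use in matching.
- **Socioeconomic status is adjusted for**, which covers part of any regional difference in social structure. It does not cover differences in local supply or coding.
- **Adjustment is not free for the programme effect.** If place is closely tied to exposure, conditioning on it uses up exposure contrast. This stands and is costed below.

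**Conclusion.** The mismatch is real and worth correcting. District is important enough to match on but is absent from the stated adjustment set. In the unmatched whole cohort, place is therefore handled neither by design nor by the stated model. For the programme effect, birth-weight matching gives no protection and no stated covariate supplies it.

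The size is not fixed by the documents. With 20 to 30 % of families near the centre, exposure of 30 to 60 % there and 2 to 5 % elsewhere, a 0.10 SD regional difference yields 0.04 to 0.08 SD of spurious programme effect. All these inputs are assumptions, and the direction of the bias is unknown.

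Two stronger readings fail. A regional difference does not pass almost fully into the programme effect: on these inputs 44 to 79 % of it does. Nor should the bias be set against 0.086 SD, which belongs to the LBW versus control contrast. Against the detectable programme effect of about 0.16 to 0.21 SD, it is a fifth to a half at D = 0.10. For the linked birth-weight comparison the effect is about 0.01 SD under the stated illustration, which is minor.

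**What to change.** 1. Add administrative district as a categorical covariate to the adjustment set in the Statistical analysis section, for both whole-cohort and linked models. Derive it at matching and keep it in the analysis file. If it cannot be kept, use region from the three-digit ZIP code.
2. State the covariates of the programme-effect models. Report the programme estimate with and without district.
3. Tabulate exposure by district before fitting, to see whether exposed and unexposed families overlap within districts. Births from 2007 and a programme start in 2009 leave some contrast within the programme's own district, but birth year is also in the model, so the overlap should be shown rather than assumed.

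**Cost.** For the birth-weight models it is negligible: detectable f stays at about 0.044 with up to 28 extra degrees of freedom. For the programme effect the standard error rises by about 6 to 36 % under the assumed exposure ranges, which is why both estimates should be reported. No new data collection is needed if the place variable already used for matching is retained.

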**Fig. 2 Fig2:**
[figure not shown]
Study flow chart

### Instruments

The following instruments will be used as part of the primary data collection to assess parental stress, parent-child-relationship, mental development and quality of life. These tests are widely used, valid, reliable, and available in German language:parental stress and parentchild relationshipEBI [Eltern-Belastungs-Inventar] (german version of PSI [Parenting stress index]); Tröster H 2011 [43].mental development of childrenSDQ [Strengths and Difficulties Questionnaire]; Goodman R 1997 [44].quality of lifeparents: WHOQOL-BREF [WHO-Quality of Life—brief version]; Angermeyer MC et al. 2000 [45].children: KINDL [Questionnaire for the collection of health-related quality of life in children and adolescents]; Ravens-Sieberer U, Bullinger M 1998 [46].

These instruments are incorporated into the study questionnaire after having obtained the respective author licenses. At the timepoint of submission of this study protocol, all necessary licenses had been obtained.

To meet the goal of assessing potential consequences of preterm birth not covered with these instruments (e.g. school performance, details on physical development) as well as details on psychosocial care in the neonatal period, the study questionnaire will also contain items developed by the authors and the scientific advisory board. The study questionnaire will be beta-tested and revised if necessary prior to application.

### Procedures of data collection

The fundamental principle of the data concept, which will be outlined below, is to strictly separate the sites of data collection from the data analysis site.

Starting point is the site of data collection I (AOK PLUS), which submits pseudonymized (pseudonym I) outpatient and inpatient data of all children born in Saxony between January 2007 and December 2013 with health insurance at the AOK PLUS to the data analysis site (Center for Evidence-Based Healthcare (ZEGV)).

Data analysis site (ZEGV) will then identify individuals eligible for the primary data collection and gives pseudonyms (pseudonym I) of all VLBW and LBW children as well as of matched control children to the site of data collection I (AOK PLUS). For reasons of better practicability, ZEGV additionally transfers a new short pseudonym per individual (pseudonym II).

Data collection site I (AOK PLUS) de-pseudonymizes these information and sends questionnaires with pseudonym I and II to the parents or legal caregivers of the selected AOK PLUS members. Each questionnaire is supplemented by a) a detailed study information explaining study objectives, study design and data protections issues, and b) an informed consent form.

AOK PLUS members whose caregivers agree with study participation send the completed questionnaire and the signed consent form to the data collection site II (KKS).

The data collection site II (KKS) will receive the completed questionnaires and consent forms. Only questionnaires accompanied by a validly signed consent form will be considered for the study. KKS will delete any personal identifiers from those datasets, pseudonymize them and send them to the data analysis site (ZEGV) for the linkage with administrative data and statistical analysis. Throughout the study, the site of data analysis (ZEGV) will only use pseudonymized data.

The process of data collection is summarized in Fig. 3.

**Fig. 3 Fig3:**
[figure not shown]
Data collection and data flow

### Data preparation

The classification into different birth weight groups (VLBW, LBW and controls) is based on documented birth weight and assigned directly by the health insurance company. In the absence of a documented birth weight, ‘unknown birth weight’ is encoded by the insurance. In order to limit the number of children in this group, those children will be reassigned by the authors according to the child`s inpatient or outpatient P07-ICD-diagnoses which directly refer to a specific birth weight (ICD-10-GM P07.0-, P07.00, P07.01, P07.02, P07.10 or P07.11^1^^a ^lead to reassignment to the VLBW-group; P07.1- or P07.12^b^ lead to reassignment to the LBW-group).

In case there is none of the mentioned birth weight specific diagnoses it will be checked whether a hospital admission within the first 7 days after birth has been coded and a documented admission weight is available. If both criteria are fulfilled, the child will be reassigned in accordance with the given admission weight to the VLBW, LBW or control group.

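### For children of unknown birth weight, the unspecified code P07.1- is sent to LBW although it spans VLBW and LBW, and it blocks use of a recorded admission weight

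*Protocol article*

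**What the plan says.** Under Data preparation, the insurer normally assigns the class from the recorded birth weight. The rules at issue apply only "In the absence of a documented birth weight", when the insurer codes the weight as unknown. They have two steps.

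- **Step 1, diagnoses.** The plan uses inpatient or outpatient "P07-ICD-diagnoses which directly refer to a specific birth weight". The VLBW list is "ICD-10-GM P07.0-, P07.00, P07.01, P07.02, P07.10 or P07.11". The LBW list is "P07.1- or P07.12".
- **Step 2, admission weight.** "In case there is none of the mentioned birth weight specific diagnoses it will be checked" whether the child was admitted to hospital in the first 7 days and has a recorded admission weight. If so, the child is "reassigned in accordance with the given admission weight to the VLBW, LBW or control group".

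Design and recruitment sets the class limits at below 1,500 g (VLBW), 1,500 to 2,499 g (LBW) and 2,500 g or more (controls). It expects about 1,000 VLBW and 5,500 LBW children. Statistical analysis uses these three classes as the levels of the main exposure.

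**The concern.** The plan justifies step 1 by saying that the chosen codes point to a specific birth weight. P07.1- does not do so at the 1,500 g limit. The plan nevertheless lets it decide the class, and by doing so skips the one further piece of recorded information that the plan itself accepts for assigning a class.

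At stake is the separation of the two lower levels of the main exposure. Any error from this code runs one way, from VLBW into LBW. If VLBW children do worse and cost more, as the study's hypothesis on preterm birth suggests, the LBW group will look somewhat worse against controls than it should.

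**Working it through.** **1. Mapping.** The codes as the article prints them:

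| Code | Assigned class | Do its listed sub-codes agree? |
|---|---|---|
| P07.0- | VLBW | Yes: P07.00, P07.01 and P07.02 all go to VLBW |
| P07.10, P07.11 | VLBW | specific code |
| P07.12 | LBW | specific code |
| P07.1- | LBW | No: two sub-codes go to VLBW, one to LBW |

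The unspecified P07.0- is harmless because every branch under it ends in VLBW. P07.1- is different. Reading the dash as a wildcard does not help, since P07.10 and P07.11 would then fall under both lists.

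**2. Gate.** Step 2 is reached only if none of the listed codes is present, and P07.1- is listed. Take a child of unknown birth weight whose only listed code is P07.1- and whose recorded admission weight on day 1 is 1,200 g (an invented example). Step 1 assigns LBW and step 2 is not run. Without the P07.1- code, the same child would be assigned VLBW.

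**3. Share of P07.1--only children who are VLBW.** The article states no figure to reproduce. Inputs are the expected 1,000 VLBW and 5,500 LBW children. Assume that a missing last digit is equally likely in both classes, and let s be the fraction of VLBW children in the P07.1 range rather than P07.0. The documents do not give s.

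Share = 1,000s / (1,000s + 5,500)

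- s = 0.40: 400/5,900 = 6.8%
- s = 0.50: 500/6,000 = 8.3%
- s = 0.67: 670/6,170 = 10.9%
- s = 1 (upper bound): 1,000/6,500 = 15.4%

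**4. Children misplaced.** Let U be the number of unknown-weight children whose only listed code is P07.1-. U is not given, so the values below are assumptions. Misplaced k = U × share:

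| U | share 6.8% | share 10.9% | share 15.4% |
|---|---|---|---|
| 100 | 7 | 11 | 15 |
| 500 | 34 | 54 | 77 |
| 1,000 | 68 | 109 | 154 |

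For k = 7, 54 and 154, this is 0.7%, 5.4% and 15.4% of the 1,000 VLBW children.

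**5. Effect on LBW against controls.** Let V and L be the true VLBW and LBW means of an outcome, and m the mean of the moved children. The LBW mean shifts by k(m − L)/(5,500 + k). As a fraction of the gap m − L this is 7/5,507 = 0.13%, 54/5,554 = 0.97% and 154/5,654 = 2.7%. The shift is towards worse outcomes if the moved children do worse than LBW children.

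**6. Effect on VLBW against LBW.** Let d = V − m, with higher values worse. The remaining VLBW mean rises by kd/(1,000 − k), while the LBW mean rises as in step 5. The contrast widens when d/(1,000 − k) > (m − L)/(5,500 + k). Since m − L = (V − L) − d, this reduces to d/(V − L) > (1,000 − k)/6,500. The threshold is 993/6,500 = 15.3% for k = 7, 946/6,500 = 14.6% for k = 54 and 846/6,500 = 13.0% for k = 154. If the moved children lie further than that from the VLBW mean towards the LBW mean, the contrast widens; otherwise it shrinks.

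**The case against.** **LBW is the likelier class.** This is true: under proportional coding at least 85% of these children are LBW. It supports LBW as the fallback when nothing else is recorded. It does not support overriding a recorded weight.

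**Admission weight is only a proxy.** A weight taken up to 7 days after birth can differ from birth weight, so near 1,500 g it may not settle the class. That stands as a limit on the fix. But the plan already accepts this weight for children with no listed code, and it tells more about the 1,500 g limit than a code that covers both sides of it.

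**The scope is narrow.** This also stands. The insurer assigns most children from documented weight, and the rule reaches only those with unknown weight. Controls are not touched by this error. Nor is selection for the questionnaire, since families of all VLBW and LBW children are approached. A reader might infer that the exposure is materially misclassified in every analysis. The variable is used throughout, but the documents do not support an error of that extent.

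**Other P07 codes do not close the gate.** A reader might take the admission-weight step to require the absence of any P07 code. The text requires only that none of the listed codes is present.

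**Detail may sit in the full plan.** The article gives no order for a child with P07.1- in one record and P07.10 in another. A condensed article may leave that out, so it is not counted here. The assignment of P07.1- is different, because the article states it outright. The footnotes to the code lists are not shown; they would matter only if they stated an exception.

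**Conclusion.** The point holds as a small, avoidable flaw in a stated rule. By the plan's own mapping P07.1- does not identify a class at 1,500 g, yet it decides the class and shuts out the admission weight.

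The size cannot be determined from the documents. The bound of about 15% VLBW among P07.1--only children rests on the plan's approximate class sizes and on unspecified coding being equally likely in both classes. With 100 to 500 such children and shares of 6.8% to 10.9%, 7 to 54 VLBW children would be misplaced, and the LBW mean would move by about 1% or less of the gap between the moved children and true LBW children. Only those with a recorded admission weight or a specific code could be recovered.

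The LBW-control comparison tends to be overstated, provided the moved children do worse than LBW children. A reader might also infer that the VLBW-LBW contrast must shrink. The documents do not support that. The children moved come from the P07.1 range and may be closer to LBW than the average VLBW child. If they lie more than about 15% of the way from the VLBW mean to the LBW mean, the contrast widens.

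**What to change.** Do not let P07.1- alone decide the class. For a child of unknown birth weight who carries it:

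1. If any record holds a specific code (P07.0-, P07.00 to P07.02, or P07.10 to P07.12), use that code.
2. Otherwise use the admission weight from the first 7 days, as step 2 already provides. Use it here only to choose between VLBW and LBW, since no listed P07.1 sub-code leads to the control group.
3. If neither exists, keep LBW as the likelier class and run a sensitivity analysis that excludes these children.

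Report how many children fall under each step, so that the size of the issue becomes known.

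This keeps the plan's aim of leaving few children unclassified and uses fields the plan already relies on. The cost is slightly more algorithm work and one sensitivity analysis. The remaining weakness is that admission weight is a proxy for birth weight, which matters for children near 1,500 g.
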